### Outcome measures

#### Primary outcome

The primary outcome of this study is the symptom burden in patients with lung cancer during the first-line combination immunotherapy course. It will be assessed using the MDASI-LC and symptomatic irAEs scale directly from patient self-reports. MDASI-LC [17], the lung cancer-specific PRO measurement, will be translated into simplified Chinese to collect longitudinal symptom data once before treatment (typically within 3 days before treatment) and weekly throughout the treatment and till 1 month after treatment completion. It comprises 16 symptoms (pain, fatigue, nausea, disturbed sleep, distress, short breath, remember things, lack of appetite, drowsy, dry mouth, sad, vomiting, numbness, cough, constipation, and sore throat) and six functional items (activity, mood, work, relations, walking, and enjoy life). Each item uses a 0-10-point scale, with 0 representing “symptom has not been present or no functional impairment” and 10 representing “the most severe symptoms or functional impairment”. In addition, the symptomatic irAE scale is a subgroup of symptomatic irAE items from the Patient Reported Outcomes version of the Common Terminology Criteria for Adverse Events library [18, 19], which provides a valid and reliable assessment of symptomatic toxic effects from the patient’s perspective, and is encouraged for use in oncology trials to enhance the accuracy of adverse event reporting [19]. The scale consisting of 15 items (bellyache, diarrhea, bloated pain, night sweats, headache, rash, chills and fever, pruritus, pectoralgia, hemoptysis, abdominal, early satiety, taste change, smell change, and palpitation) will be translated into Chinese to collect the severity score of irAEs. Like the MDASI-LC, it also uses a 0–10 scale, where 0 represents “symptom has not been present or no functional impairment” and 10 represents “the most severe symptoms or functional impairment”.

#### Secondary outcome

The secondary outcomes will include the incidence rate of grade 3–4 immunotoxicity, the completion rate of six cycles of immunotherapy, the timeliness of treatment, complication rate, and unplanned clinic rate. Immunotoxicity will be assessed based on the Common Terminology Criteria for Adverse Events (CTCAE v.5) criteria, and irAEs will be classified according to the affected system, including respiratory, gastrointestinal dermatological, hepatic, articular, neurological, and endocrine systems.

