### Withdrawal criteria

Participants will be withdrawn from the study, and no further data will be collected if they meet the criteria, as shown in Table 2.

**Table 2 Tab2:** The withdrawal criteria for the study

Withdrawal criteria
1. Cancelling planned immunotherapy before the treatment.
2. Patients who break the study protocol (deliberately offering inaccurate PRO data).
3. Patients who demand an immediate withdraw from the research.
4. Severe complications interfering with PRO data collection.
5. Other conditions that require withdrawal as assessed by the investigator.

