#### Exploratory outcome

The exploratory outcomes will include overall survival (OS) and progression-free survival (PFS). PFS and OS are defined from start of treatment until recurrence or date of death.

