### Data analysis

Participants who meet the withdrawal criteria for the study will not be included in the final analysis. For the study results, descriptive analysis will be undertaken by using mean ± SD or median with interquartile range (IQR) for continuous variables, and absolute number (n) and proportion (%) for categorical variables. First, we will use descriptive statistics to describe the severity and time trend of symptom burden and functional interference in patients treated with combination immunotherapy. Symptom trajectories will be depicted with line graphs describing the severity score of patients reporting symptoms from pre-treatment to complete the whole treatment course for 1 month. Furthermore, the association between symptom and clinical outcomes will be examined. Specifically, the symptoms will be categorized based on the severity, and the difference in clinical outcomes (including incidence rate of grade 3–4 immunotoxicity, the completion rate of six cycles of immunotherapy, the timeliness of treatment, complication rate, unplanned clinic rate, OS and PFS) will be assessed. We will use R v.4.2.0 to perform the statistical analysis, and differences will be considered statistically significant if the two-tailed *p*-values are < 0.05.

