## Discussion

Cancer and its treatments often cause multiple symptoms in patients, negatively influencing their prognosis and contributing to physical and psychological consequences [20]. Treatment-related adverse events severely affect prognosis in most cases, and the link between irAEs and prognosis is complicated and related [21]. Although irAEs with delayed onset and prolonged duration are easily neglected [22], organ injury or death resulting from irAEs can have a detrimental effect on patient survival [23], and permanent ICIs cessation due to irAEs can adversely affect treatment benefits [24]. It is therefore evident that symptoms of patients with cancer after treatment with immunotherapy need to be followed up effectively and completely. Electronic patient-reported outcomes (ePROs), which comprise health-related questionnaires completed by the patient themselves, are a promising approach for follow-up and can effectively detect symptoms and their severity. Additionally, as a new follow-up model, it has been reported to be timely and cost-effective and employs a longitudinal collection of patient-symptom data [25] .

Therefore, this study is focused on the assessment of the symptoms following combination immunotherapy, through the application of the ePRO model. Potential implications of the findings include [1] identifying the targeted symptoms for patients with advanced lung cancer receiving first-line combination immunotherapy; [2] demonstrating the longitudinal symptom trajectories of first-line combination immunotherapy for lung cancer; and [3] examining the correlation between symptom burden and clinical outcomes (including incidence rate of grade 3–4 immunotoxicity, the completion rate of six cycles of immunotherapy, the timeliness of treatment, complication rate, unplanned clinic rate, OS and PFS).

ePROs are a novel and significant way to clinically follow up symptoms after treatment with immunotherapy by focusing on patients’ views and experiences. Using this method, this study will help understand symptom trajectories following combination immunotherapy, which is important in improving preparedness for immunotherapy treatment as well as setting up individual strategies to optimize patient experience and outcomes.

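### The immunotoxicity outcome stops at grade 4, so a fatal irAE with no earlier grade 3–4 record is not counted and the high-grade rate is understated

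*Protocol article*

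**What the plan says.** The Secondary outcome section lists the "incidence rate of grade 3–4 immunotoxicity" first among five secondary outcomes and names the scale: "Immunotoxicity will be assessed based on the Common Terminology Criteria for Adverse Events (CTCAE v.5) criteria". The Data analysis section carries the same range into the association analysis: "the symptoms will be categorized based on the severity, and the difference in clinical outcomes (including incidence rate of grade 3–4 immunotoxicity" and the other outcomes are compared across the symptom categories. The Discussion repeats the range when it lists the study's expected contributions.

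Three other statements bear on a fatal event:

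- The Discussion recognises that such events occur: "organ injury or death resulting from irAEs can have a detrimental effect on patient survival".
- Withdrawal criterion 4 (Table 2) is "Severe complications interfering with PRO data collection". The text above the table says that data collection stops for anyone who meets a criterion. Data analysis adds: "Participants who meet the withdrawal criteria for the study will not be included in the final analysis".
- Deaths otherwise enter only through overall and progression-free survival, which are exploratory. Nothing there separates deaths due to an irAE from other deaths.

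No section widens the range to grade 3 or higher, mentions grade 5, or says how a fatal irAE is counted.

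**The concern.** On the CTCAE scale a death related to the adverse event is grade 5. An outcome limited to grades 3 and 4 therefore omits the worst category of its own scale. The study wants to show what symptom burden leads to and to help clinicians recognise dangerous irAEs, and a fatal irAE is the consequence that matters most for that purpose.

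Two results are at stake. One is the reported rate of high-grade immunotoxicity. The other is the comparison of that rate across symptom-severity categories, where few events are likely and a handful of misplaced patients can shift the estimate.

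**Working it through.** The article states no expected grade 3–4 or grade 5 rate, so there is no figure to reproduce. The check has three steps. All rates below are assumptions.

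**Step 1. Where can a patient with a fatal irAE end up?**

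| Route | Basis in the article | Result under grade 3–4 |
|---|---|---|
| A. Analysed, only high-grade record is grade 5 | Secondary outcome, read literally | Non-case |
| B. Withdrawn under criterion 4 | Withdrawal criteria with Data analysis | Not in numerator or denominator |
| C. Grade 3 or 4 recorded before death | Possible; the article does not say whether worst grade or any grade counts | May already be a case |

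Routes A and B lose the event. Route C may not.

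**Step 2. How far is the rate understated?**

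Inputs: planned sample 168 and dropout 20% (Sample size calculation), so 168 × 0.8 ≈ 134 evaluable. Assumed: fatal irAE share f = 0.5% to 3%; grade 3–4 share g = 10% to 20%, counting only patients without a fatal irAE. Route C is set to zero, which gives the upper bound.

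Patients affected: 134 × 0.005 = 0.7 to 134 × 0.03 = 4.0.

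Route A: reported rate g, true rate g + f, relative shortfall f/(g + f).

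Route B: reported rate g/(1 − f), relative shortfall 1 − [g/(1 − f)]/(g + f). This is positive whenever g + f is below 1.

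| g | f | Rate, grade 3 or higher | Shortfall, route A | Shortfall, route B |
|---|---|---|---|---|
| 10% | 0.5% | 10.5% | 0.005/0.105 = 4.8% | 1 − 0.1005/0.105 = 4.3% |
| 10% | 3% | 13% | 0.03/0.13 = 23% | 1 − 0.1031/0.13 = 21% |
| 20% | 0.5% | 20.5% | 0.005/0.205 = 2.4% | 1 − 0.2010/0.205 = 2.0% |
| 20% | 3% | 23% | 0.03/0.23 = 13% | 1 − 0.2062/0.23 = 10% |

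Both routes understate the rate, by similar amounts.

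**Step 3. What happens to the association?**

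Illustration: two symptom groups of 84 with assumed true rates of grade 3 or higher of 15% and 8%. Expected events are 12.6 and 6.72, and the odds ratio is (12.6/71.4)/(6.72/77.28) = 2.03. Take fatal irAEs as 1% or 2% of 168, that is 1.68 or 3.36 expected deaths.

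| Where the deaths fall | Handling | OR, 1% fatal | OR, 2% fatal |
|---|---|---|---|
| All in the high-burden group | Coded as non-cases | 1.72 | 1.42 |
| All in the high-burden group | Excluded | 1.76 | 1.49 |
| Split equally | Coded as non-cases | 2.16 | 2.34 |
| Split equally | Excluded | 2.16 | 2.35 |

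Worked example, first row at 1%: (10.92/73.08)/(6.72/77.28) = 1.72. Third row at 1%: (11.76/72.24)/(5.88/78.12) = 2.16.

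The odds ratio falls below 2.03 when the deaths sit in the high-burden group and rises above it when they are split equally. The sign of the bias is not fixed.

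**The case against.** A reader might infer that every patient with a fatal irAE is placed with the patients free of severe toxicity, and that this pulls the association with symptom burden toward the null. The documents do not support either step. No section says that fatal cases become non-cases; criterion 4 with the exclusion of withdrawn participants may remove them, and an earlier grade 3 or 4 record may already count them. The pull toward the null requires fatal cases to have high symptom scores, and the article gives no evidence of that. It describes irAEs as sometimes sudden, and symptoms are collected weekly, so the last score before death need not be high. This part of the objection stands in full.

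It can also be said that the outcome measures exactly what it names, that reporting grades 3–4 apart from deaths is legitimate, that survival captures the deaths, and that a condensed article leaves counting rules to the full protocol. This stands only in part. The range is a stated definition, given in three sections, and is not a detail left open. Survival counts deaths from any cause, so it does not recover the irAE deaths. Separate reporting would be sound if grade 5 had its own count, but the article provides none.

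Finally, the counts are small and every rate is assumed, for one of five secondary outcomes in an observational cohort. That is correct, and it limits the weight of the point.

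**Conclusion.** The point holds as a minor one. The outcome omits grade 5 wherever it is defined or used, although the article acknowledges death from irAEs. A patient whose only high-grade record is fatal is lost from the numerator, either as a non-case or through withdrawal, so the rate of high-grade immunotoxicity is understated. That conclusion needs no assumption about rates.

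The size does. With fatal shares of 0.5–3% and grade 3–4 shares of 10–20%, about 0.7–4 of 134 patients are affected and the relative undercount is at most about 2–23%. It is smaller if some of them had an earlier grade 3–4 record that counts. The association with symptom burden may be biased, but neither the direction nor the amount can be stated from the article.

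**What to change.** In Secondary outcome, Data analysis and Discussion, replace the grade 3–4 range with grade 3 or higher (grades 3–5), classified by each patient's worst grade. Report the number of grade 5 events separately, so that a grade 3–4 count remains available.

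The wording change alone would not recover patients lost through withdrawal. State also that a patient with a fatal irAE stays in the analysis of this outcome even if criterion 4 has ended that patient's questionnaire collection, and that toxicity grades continue to be recorded for this purpose.

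The cost is small: a few sentences, with CTCAE grading and dates of death already part of the planned data. The one added task is to attribute each death to an irAE or to another cause when grades are assigned, which the article does not currently describe.

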## Background

Lung cancer is the second most common malignancy and most lethal cancer worldwide, with highest morbidity and mortality rates in China [1]. Many patients with lung cancer are already in the advanced stages at initial clinical diagnosis, thereby having poor prognosis and a relatively short overall survival. Cancer immunotherapy, especially immune checkpoint inhibitors (ICIs), is an emerging therapeutic strategy, and combination therapy with traditional chemotherapy or radiation therapy has played an important role in the treatment of advanced lung cancer. It has markedly improved the survival of some patients, and a significant fraction of patients can achieve long-term survival of ≥ 5 years [2]. Therefore, regarding ICIs, the quality of life of patients with long-term survival is extremely important. Combination immunotherapy for lung cancer is associated with significant treatment-related symptoms [3]. Therein, irAEs following ICIs generally have a long duration and broad spectrum [4] and can cause physical and psychosocial burdens on patients, thereby negatively affecting quality of life and compliance with therapy.

Symptoms in patients with lung cancer receiving immunotherapy are traditionally assessed by the medical staff rather than self-reports from patients [5, 6]. PRO (patient-reported outcome) is a non-traditional clinical indicator of capturing patient symptoms, functional outcomes, or health-related quality of life directly from the patients’ perspective without interpretation from others [7, 8]. Screening of PRO followed by tailored interventions can achieve better clinical outcomes [9]. In patients with advanced lung cancer, much attention has been focused on tracking adverse event symptoms induced by chemotherapy, which showed significant survival benefits when combined with threshold-driven alter and response [10, 11].

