However, the longitudinal symptom trajectories after immunotherapy treatment in patients with advanced lung cancer have not been addressed yet. Particularly, immunotherapy is a new treatment paradigm and can lead to complex irAEs with relative specificity. Addition of PROs to traditionally collected outcomes can provide a comprehensive overview of patient experience during and after treatment [9]. It is, therefore, necessary to track the symptom trajectories after immunotherapy treatment directly from patient self-reports. Moreover, the current understanding of the association between patient-reported symptoms following immunotherapy and clinical outcomes is limited, and only a few indicators (e.g., overall survival and progression-free survival) have been reported [12]. The connection between symptom burden and clinical outcomes, including the completion rate of immunotherapy, timeliness of treatment, complication rate, and unplanned clinic rate may be critical for clinicians to manage adverse events.

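### Six-cycle completion is not separated by reason for stopping, so its association with symptom burden cannot by itself inform adverse-event management

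*Protocol article*

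**What the plan says.** The Secondary outcome section of the protocol article lists, after severe immunotoxicity, "the completion rate of six cycles of immunotherapy, the timeliness of treatment, complication rate, and unplanned clinic rate". Completion appears there, in Data analysis and in the Discussion as a single rate. None of these places divides it by reason for stopping.

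The Data analysis section fixes how it is used: "the symptoms will be categorized based on the severity, and the difference in clinical outcomes" will be assessed, and six-cycle completion is one of the outcomes named. No split by reason and no allowance for disease course is mentioned.

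The Background gives the purpose. Of the outcomes to be connected with symptom burden, it says: "including the completion rate of immunotherapy, timeliness of treatment, complication rate, and unplanned clinic rate may be critical for clinicians to manage adverse events". The Discussion adds that permanently stopping immunotherapy because of immune-related events can reduce its benefit. The Background also describes patients diagnosed at an advanced stage as "thereby having poor prognosis and a relatively short overall survival".

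Two further rules affect who is counted. The Data analysis section states: "Participants who meet the withdrawal criteria for the study will not be included in the final analysis". The Withdrawal criteria include "Severe complications interfering with PRO data collection" and "Other conditions that require withdrawal as assessed by the investigator". Progression is not a listed criterion.

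**The concern.** The protocol's interest is in symptoms as signals of treatment toxicity. An undivided completion rate mixes at least two processes: stopping because treatment was not tolerated, and stopping because the cancer progressed or the patient died.

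The second process can also raise the exposure. The MDASI-LC asks about pain, cough, shortness of breath, fatigue and lack of appetite, and a growing tumour can produce all of these. Disease course can then drive both the symptom category and the failure to reach six cycles. The result can go wrong in two directions: an association may appear when toxicity does not differ at all, or a real link between symptoms and toxicity stops may be diluted. In both cases a reader who follows the Background would take the result as guidance on adverse events.

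**Working it through.** **The plan's own figure.** The documents give no figure for completion. The only design figure is the sample size of 168. With 30:70 groups, means 1.6 and 1.0, SDs 1.1 and 0.7, two-sided 5% and 90% power:

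N = (1.960 + 1.282)² × (1.1²/0.3 + 0.7²/0.7) / 0.6² ≈ 138

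Allowing for 20% dropout gives 138.2/0.8 ≈ 173 or 138.2 × 1.2 ≈ 166, so 168 is reproduced closely. The point does not depend on it. From it, 168 × 0.8 ≈ 134 evaluable patients, or 67 per group if the two symptom groups are taken as equal (an assumption).

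All stopping rates below are assumptions. They show direction and possible range and do not predict this cohort.

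**1. Early progression could be common.** Assume 3-week cycles (15 weeks, 3.45 months, from cycle 1 to cycle 6) and exponential time to progression or death.

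P = 1 − exp(−ln2 × 3.45 / median)

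| Assumed median PFS (months) | P | Of 134 |
|---|---|---|
| 5 | 0.38 | 51 |
| 8 | 0.26 | 35 |
| 12 | 0.18 | 24 |

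Not every such patient need stop treatment at once, so these are rough upper counts.

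**2. An association can arise with equal toxicity.** Let toxicity stop 10% in both groups, and let progression or death stop 20% of the low-symptom group. Completion = 1 − 0.10 − progression or death.

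| Progression or death, high-symptom group | Completion, low vs high | Ratio | Chance of p<0.05, 67 per group |
|---|---|---|---|
| 20% | 70% vs 70% | 1.00 | no true difference |
| 30% | 70% vs 60% | 0.86 | about 23% |
| 40% | 70% vs 50% | 0.71 | about 66% |

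Split by reason, the toxicity stops are 10% against 10% in every row.

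**3. A real toxicity link can be diluted.** Let toxicity stop 5% of the low and 15% of the high group (risk ratio 3.0), with progression stopping the same share of both, independently. Non-completion = 1 − (1 − toxicity)(1 − progression).

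| Progression, both groups | Low | High | Risk ratio |
|---|---|---|---|
| 20% | 0.240 | 0.320 | 1.33 |
| 30% | 0.335 | 0.405 | 1.21 |
| 40% | 0.430 | 0.490 | 1.14 |

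This case shows dilution only, because progression is held equal. Case 2 shows the opposite error.

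**4. The exclusions do not separate the reasons.** A severe complication that interferes with reporting can take a toxicity stop out of the analysis. Progression is not listed, so these patients leave only if the investigator uses the open criterion. The first route would shift the remaining non-completions towards progression, while the second could remove some progressions. The net effect cannot be determined from the text.

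**5. Precision of a toxicity-specific outcome.** At 5% and 15% of 67 per group there are about 3.4 + 10.1 ≈ 13 events, ignoring competing stops. The standard error of the log risk ratio is √(1/3.35 − 1/67 + 1/10.05 − 1/67) ≈ 0.61. A risk ratio of 3.0 then has a 95% interval of 3.0 × exp(±1.96 × 0.61), about 0.9 to 9.9.

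**The case against.** The strongest reply is that the article only names the outcome. A reader might infer that the protocol has a rule counting progression, death and toxicity alike. It has no such rule. It is silent on reasons, and a full protocol or analysis plan not shown may define the outcome further. The withdrawal rules may also take some toxicity or progression cases out of the comparison. This stands, and the point is limited accordingly: the rate is undivided as listed, and no separation is planned where its analysis is described.

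A reader might also infer that completion is offered as a measure of tolerability and so fails at its task. No section calls it that. The stated aim is association with clinical outcomes, and all-cause completion is a legitimate one. Severe immunotoxicity is captured separately, as are PFS and OS. This stands as a reason to keep the outcome. It does not remove the difficulty, because the Background names completion among the outcomes whose link with symptoms should help in managing adverse events.

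The symptomatic irAE scale adds items such as rash, pruritus and diarrhoea that point less to the tumour. That helps, but the MDASI-LC remains part of the primary measure, and the added scale itself includes haemoptysis and chest pain.

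A further inference would be that patients prescribed fewer than six cycles are counted as failures. The documents do not say that such patients are enrolled, so nothing is claimed on this.

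**Conclusion.** The point holds in limited form. Six-cycle completion is compared across symptom-severity groups without separating reasons for stopping. Tumour symptoms and early stopping can share a cause, so an association with symptom burden may reflect disease course and cannot on its own support conclusions on adverse events.

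The documents do not determine the size. Under the assumed rates, completion could differ by 20 percentage points with identical toxicity, or a threefold toxicity ratio could shrink to between 1.33 and 1.14. Both depend on invented stopping rates, and the two group sizes are also assumed. It would be wrong to conclude that the completion result will be misleading, or that the outcome should be dropped. The matter concerns the interpretation of one secondary outcome of an observational cohort. It is a worthwhile, inexpensive improvement, and neither the primary outcome nor the sample size is affected.

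**What to change.** - Record one primary reason for each stop before cycle six: toxicity, progression, death, patient choice or other.
- Keep all-cause completion of six cycles as listed.
- Add an analysis of symptom burden against stopping for toxicity before cycle six, with progression and death as competing events.
- In that analysis, count patients who stop because of severe complications as events instead of dropping them as withdrawals. The date and reason of the stop must therefore be kept for them.
- Base any conclusion on adverse-event management on this added analysis, reported with its confidence interval.

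The cost is one coded field in REDCap, partly filled retrospectively because recruitment is under way, and less if the form already holds the reason. The real downside is few toxicity events (about 13 under the assumed rates), so the estimate will be imprecise. It should stand beside the all-cause rate and not replace it.
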